***Hypothesis 1 – Clinical recovery:***

Individuals in the SAEP will have lower symptom scores and faster return to asymptomatic status, leading to shorter clinical recovery times compared to those in usual care group.

**Specific Aim 2:** To determine the effect of an SAEP in concussed subjects on ANS function, blood biomarkers, and cognition.

***Hypothesis 2a*** – Cardiovascular responses:

Compared to the SAEP, the usual of care group will display lower HRV and BPV at days 14, 21, and 28 post-SRC.

***Hypothesis 2b:*** *- Peripheral blood biomarkers:*

As compared to the usual of care group, the SAEP group will display higher peripheral concentrations of neuroreparative indices BDNF and PRDX-6, lower concentrations of the CNS-injury analogue GFAP, lower concentrations of the inflammatory marker MCP-1, and lower resting peripheral catecholamine levels.

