# 13.0 SAMPLE SIZE

Sample size was determined from a power analysis incorporating published data by our group on days to medical clearance in high school patients evaluated at the MacIntosh Clinic (mean time to clearance = 43 days, SD = 20 days).^79^. Hence, to reduce time to medical clearance to 36 days (delta = 7), at a significance level of 0.05 and a at a moderate effect level (0.7), would require 53 participants per group.

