## 14.2 Analysis of Secondary Endpoints

Furthermore, A mixed model ANOVA will be used to evaluate possible differences in symptoms, HRV, BPV, cognitive performance and blood biomarkers between the standard of care group and AE intervention group (between group analysis) across 6 time points; 7, 14, 21, 28, and 90 days post-SRC (within group analysis). If the data fails the required normality assumption, the appropriate transformation will be performed on all data. We expect approximately 40% females in our study sample, allowing for differential responses between males and females. We will perform separate Kaplan Meier analyses in males and females on time to medical clearance between the standard of care and AE intervention groups. Likewise, we will perform separate mixed model ANOVA analyses in males and females to evaluate differences between AE intervention and standard care groups for all aforementioned secondary measures.

Regarding blood biomarker analysis, each individual biomarker will only be included for statistical quantitation if they fall within the lower and upper limits of quantitation (LLOQ and ULOQ, respectively) as delineated by the manufacturer. All samples will be run in duplicate, and excluded if the coefficient of variance (CV) between duplicate samples is > 25%. Furthermore, mean statistical analysis will only be performed on biomarkers that have quantifiable samples in > 50%, in all groups in question. A quantifiable sample is 1) within the manufacturers quantitative range, and 2) displays a CV between duplicates of < 25%. In instances where one or both groups contain <50% quantifiable samples, differences between these groups will be evaluated by χ^2^.

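### The fallback χ² for poorly quantified biomarkers pools low, high and imprecise samples into one class, so depending on why samples fail it can lose nearly all power for Hypothesis 2b and leave the direction unreadable

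*Protocol*

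**What the plan says.** Section 8.0, Hypothesis 2b, is directional and about level: the exercise arm is expected to show "higher peripheral concentrations of neuroreparative indices BDNF and PRDX-6, lower concentrations of the CNS-injury analogue GFAP", with MCP-1 and resting catecholamines also lower.

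Section 14.2 sets the rules for biomarker data:

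- Range: each biomarker will "only be included for statistical quantitation if they fall within the lower and upper limits of quantitation (LLOQ and ULOQ, respectively").
- Precision: "All samples will be run in duplicate, and excluded if the coefficient of variance (CV) between duplicate samples is > 25" per cent.
- Combined status: "A quantifiable sample is 1) within the manufacturers quantitative range, and 2) displays a CV between duplicates of < 25" per cent.
- Condition for comparing means: "mean statistical analysis will only be performed on biomarkers that have quantifiable samples in > 50%, in all groups in question".
- Otherwise: "In instances where one or both groups contain <50% quantifiable samples, differences between these groups will be evaluated by" χ².

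The section does not name the variable to be tabulated in the χ². It does not say that the reasons for failure will be kept apart.

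**The concern.** Quantifiable yes/no is the only binary variable in Section 14.2, and it is also the variable that triggers the fallback. The natural reading is therefore a table of arm by quantifiable status. The failing class then mixes three kinds of sample: very low values, very high values, and samples whose duplicates disagree. The first two carry information on level in opposite directions. The third may carry little or none.

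The χ² then tests whether the arms have the same proportion of passing samples. This matches a test of concentration only if failures lie on one side of the range. If they lie on both sides, a true shift takes samples out of one failing group and puts others into the opposite one, so the two movements offset each other. Precision failures unrelated to level dilute the contrast further.

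At stake is the reading of Specific Aim 2 for any marker that triggers the rule. A null χ² might say little against Hypothesis 2b, and a significant one might not show which arm had the higher concentration.

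**Working it through.** **Inputs.** From the protocol: 53 per group (Section 13.0, "would require 53 participants per group") and a significance level of 0.05. Assumed here, because the protocol gives none of it: a two-sided test, normal log-concentrations with SD 1, a true shift of d = 0.5 SD, one visit, and the mix of failure reasons. Section 13.0 sizes the trial on days to medical clearance. There is no power figure for any biomarker or for the χ², so there is nothing to reproduce on this point; 53 is used only as the planned group size.

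**Step 1: what the χ² sees.** Let l and u be the LLOQ and ULOQ on the control-arm normal scale, and c the precision-failure rate, taken as independent of level. The expected quantifiable share at shift d is

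q(d) = (1 − c) × [Φ(u − d) − Φ(l − d)].

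- 30% below and 30% above (l = −0.524, u = 0.524): q(0) = 0.400 and q(0.5) = Φ(0.024) − Φ(−1.024) = 0.510 − 0.153 = 0.357. By symmetry q(−0.5) is also 0.357, so a rise and a fall look the same.
- 60% below only (l = 0.253): q(0) = 0.400 and q(0.5) = Φ(0.247) = 0.597. A rise increases the share.
- 60% above only (u = −0.253): q(0) = 0.400 and q(0.5) = Φ(−0.753) = 0.226. The same rise lowers the share.
- 55% precision failures only: the share is 0.450 at any d, so power equals the test size.

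**Step 2: power by formula for the one-sided case.** For 0.400 against 0.597 with 53 per arm, the standard error under no difference is √(2 × 0.4985 × 0.5015 / 53) = 0.0971, and under the alternative √((0.2400 + 0.2406) / 53) = 0.0952. Power = Φ((0.197 − 1.96 × 0.0971) / 0.0952) = Φ(0.07) ≈ 53%. Simulation gives 51%.

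**Step 3: simulated power over a range of mixes.** d = 0.5, 53 per arm, 3,000 runs (Monte Carlo standard error at most √(0.25/3000) = 0.9 points). The χ² is uncorrected, on quantifiable yes/no. The comparator is a rank-sum test with below-LLOQ values lowest, above-ULOQ values highest and precision failures missing. Shares follow from the formula in Step 1.

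| Assumed failures (control arm) | Share, control → shifted arm | χ² | Rank test |
|---|---|---|---|
| 55% below | 0.45 → 0.65 | 50% | 63% |
| 55% above | 0.45 → 0.27 | 52% | 56% |
| 40% below, 20% precision | 0.48 → 0.62 | 28% | 56% |
| 30% below, 30% precision | 0.49 → 0.59 | 17% | 53% |
| 10% below, 45% precision | 0.495 → 0.53 | 6% | 44% |
| 25% below, 20% above, 10% precision | 0.495 → 0.46 | 5% | 62% |
| 30% below, 25% above | 0.45 → 0.42 | 6% | 65% |

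Independent repeat runs agree to within about two or three points. In the last row, 84% of the significant χ² results show fewer quantifiable samples in the arm with the higher concentration. In the 55% above row, all of them do.

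**Step 4: restricting to runs in which the fallback fires.** The table counts all runs. Among runs in which at least one arm had under 50% quantifiable, χ² power rises to about 62% for 55% below and 40% for 40% below with 20% precision failures. It stays at 6 to 8% in the mixes with failures at both limits and in the one dominated by precision failures.

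**The case against.** **The tabulated variable is inferred.** This is fair: Section 14.2 does not name it. The section also says that imprecise samples are excluded, which could mean that they leave before any test. But the definition of a quantifiable sample puts precision into the same status that drives the 50% rule, and nothing separates the two afterwards. A statistical analysis plan, not at hand, might set finer categories. One that follows the protocol text would inherit the pooled class.

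**The near-5% figures depend on the assumed mixes.** This also stands. With 30% below and 25% above, the assay's working range would span only 1.20 SD of log-concentration (0.524 + 0.674), and the documents do not suggest a range that narrow. Nor do they say that precision failure is unrelated to level; imprecision may well rise as concentration falls. With precision failures concentrated at low in-range values (also an assumption), χ² power in the three mixes of below-LLOQ and precision failures becomes about 43%, 39% and 36%, against 67%, 65% and 51% for the rank test. The loss remains, but power is no longer close to the test size.

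**Two stronger readings are tempting and not supported.** A reader might infer that the fallback never tests concentration and that its direction can never be read. That is wrong when failures are all below the LLOQ: the χ² then tests concentration dichotomised at that limit. With 20% quantifiable the loss almost vanishes (49% against 50%). A reader might also infer that repeated samples from one participant are pooled across visits as if independent, inflating false positives. Section 14.2 counts samples, but nowhere says that visits are pooled for the χ², so no weight is put on that here.

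**Reach is small.** Agreed. The rule affects secondary endpoints, and no figure shows that any marker will trigger it.

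**Conclusion.** The concern holds in a conditional form. The weakness is that one status pools three reasons for failure; a χ² on detectability is not in itself wrong. The cost depends on the mix of failures, which the protocol does not give:

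- Essentially all below the LLOQ: valid, readable direction, modest loss (about 50% against 63%).
- Below the LLOQ plus a substantial share of precision failures unrelated to level: power roughly halved or worse (28% against 56%; 17% against 53%).
- Both limits, or mostly precision failures unrelated to level: power of about 5 to 6%, against 44 to 65%.

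An imbalance in the pooled class cannot be turned into a direction of concentration unless the reasons for failure are known. The figures rest on a 0.5 SD shift, 53 per group at one visit, normal log-concentrations and a two-sided 0.05 test. Only secondary biomarkers that trigger the rule are affected. The change is worth making because a better analysis of the same data is available, and because choosing the categories after seeing the assay results would be data-driven.

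**What to change.** Amend Section 14.2 in two places, together, so that the definition and the test agree.

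1. **Definition.** Record range status (below LLOQ, in range, above ULOQ) separately from duplicate precision. Treat samples with a duplicate CV above 25% as missing, and leave them out of both numerator and denominator of the 50% rule. Report their number by arm, and add a sensitivity analysis in case imprecision depends on level. Changing only the χ² sentence would contradict the precision clause in the existing definition.
2. **Test.** Where under 50% of the remaining samples in either arm are in range at a visit, compare the arms at that visit by a Wilcoxon rank-sum test, with below-LLOQ values ranked lowest and above-ULOQ values highest. If χ² is kept, define its outcome as below LLOQ versus not (or above ULOQ versus not), and report the direction.

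As a safeguard, state that this analysis is done per visit or with clustering on participant.

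Cost: a wording change and a few lines of code, with no new data. The laboratory must export the reason for each failure, and results are reported as a shift in ranks rather than a simple percentage. The change should be settled before assay results are seen.

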# 15.0 INSTITUTIONAL REVIEW BOARD

We have institutional ethics approval from the University of Toronto (reference #33459) and a registered trial with clinictrials.gov (NCT02969824).

# 17.0 Appendix

**David L. MacIntosh Sport Medicine Clinic**
